## **I. Introduction / Rationale**

Psychosis is a common complication of dopaminergic treatment in Parkinson's disease, often limiting treatment of the parkinsonian motor symptoms. However, in this patient population treatment with antipsychotics, including newer agents such as risperidone and remoxipride, is generally disappointing because of intolerable motor side effects. Clozapine is thought to be an effective and generally well-tolerated treatment but does carry the important and unpredictable risk of agranulocytosis in 1%-2% of patients, some of whom may die as a result. Furthermore, there are no adequate prospective studies of clozapine in this population. These points are briefly reviewed elsewhere (Wolters et al., 1996).

Olanzapine is a recently marketed antipsychotic agent which, in studies of patients with psychosis (mostly schizophrenia), caused acute extrapyramidal side effects much less frequently than did the comparison drug haloperidol, but had similar or better efficacy. This suggests it may be better tolerated than other antipsychotic agents in patients with Parkinson's disease and psychosis.

There is one published open study of olanzapine in this population. Olanzapine was generally well-tolerated over the duration of the study, improved psychotic symptoms significantly as measured by the BPRS, and allowed a further increase in dopaminergics (and a consequent improvement in motor functioning) without marked exacerbation of psychosis (Wolters et al., 1996). However, the design of this preliminary study markedly limits the generalizability of its conclusions. Specifically, there was no placebo arm, and raters were aware both of treatment condition and duration of treatment, which may introduce substantial rater bias. Thus the efficacy of olanzapine is not definitively established in this special population.

The present study is intended to test the conclusions of the Wolters et al. study (1996) using a more rigorous approach, and extend the study questions.

## **II. Objectives**

### Primary

- 1) Determine whether olanzapine has superior efficacy to placebo in treating psychosis in patients with Parkinson's disease (PD) who are being treated with dopaminergics.
- 2) Determine whether in this setting a daily (qhs) dose of 10mg is more effective than a daily dose of 5mg.

### Secondary

- 3) Compare tolerability of 5mg and 10mg daily doses of olanzapine in this population.
- 4) Determine whether olanzapine treatment of psychosis in Parkinson's disease allows patients to take higher doses of levodopa without exacerbating psychosis.

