## **III. Investigational Plan**

### **A. Summary of Study Design**

Patients will be screened and if they meet the criteria given in section III.D.1. will enter into one of three arms, shown as three rows of the table below. Each arm will consist of nightly

(qhs) dosing of matched tablets or capsules containing 0, 5, or 10 mg of olanzapine. However, patients in the 10 mg arm will take only 5 mg nightly for the first week.

See the table below for a diagrammatic summary of the study design.

| baseline                          | 1st week | 2nd week | 2-wk visit                                                      | weeks 3-4 | 4-wk visit                                                 |
|-----------------------------------|----------|----------|-----------------------------------------------------------------|-----------|------------------------------------------------------------|
| clinical evaluation;
randomize | placebo  | placebo  | clinical evaluation;
increase
dopamimetic if
indicated | placebo   | clinical evaluation;
return to routine
clinical care |
|                                   | 5mg      | 5mg      |                                                                 | 5mg       |                                                            |
|                                   | 5mg      | 10mg     |                                                                 | 10mg      |                                                            |

Baseline evaluation:

Psychiatric, neurologic and general medical history and examination; Clinical Global Impression (CGI) by MD, PDQ39 (a brief, self-rated overall quality of life questionnaire), videotaped psychiatric interview for later blinded BPRS (Brief Psychiatric Rating Scale) rating, Schwab-England ADL assessment, full UPDRS (Unified Parkinson's Disease Rating Scale), MMSE (Folstein Mini-Mental State Examination), HDRS (Hamilton Depression Rating Scale), Beck depression inventory (Beck), patient- or caretaker-reported sleep hours/quality

Interim evaluation:

clinical evaluation; CGI (MD, pt, caretaker), videotaped psychiatric interview for later blinded BPRS, Schwab-England, full UPDRS, MMSE, pill counts, PDQ39, Beck, sleep hours

Final evaluation:

clinical evaluation; CGI (MD, pt, caretaker), videotaped psychiatric interview for later blinded BPRS, Schwab-England, full UPDRS, MMSE, pill counts, PDQ39, Beck, sleep hours

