**B. Rationale for Design and Control**

Our design can significantly strengthen the conclusions of Wolters et al. (1996) in three ways. First, with the parallel group, placebo-controlled design, we can show whether olanzapine is superior to placebo in treating PD psychosis. Second, with a fixed dose design we can address the question of optimal olanzapine dose in these patients. Third, the Wolters et al study did not use blinded ratings of psychosis. To address this, we will videotape clinical interviews at each study visit. The main outcome measure, BPRS ratings of psychosis, can then be rated after the end of the study by an investigator who will be blind not only to olanzapine dose but also to duration of treatment (0, 2, or 4 weeks). This will allow us to show that improvement in any treatment group is not due to investigator or patient expectation of improvement, and may also increase our power as the placebo group may show less change.

We chose 4 weeks rather than a longer study period because clinical experience and the Wolters et al. trial both suggest that improvement in psychosis is usually seen by this point.

The doses chosen are due in part to the desire to bracket the mean final dose in the open study (7mg/day), and in part to the fact that olanzapine is marketed in 5mg and 10mg tablets.

A placebo control is not only scientifically needed but also ethically justified, given the potential side effects of either olanzapine or other treatments of psychosis in this population (beyond the conservative measures we require for study entry).

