#### **F. Dosage and Administration**

See the summary table in III.A. for an overview. Patients who meet entry criteria will take identical study tablets nightly, containing either 5mg or 10mg olanzapine or placebo. Due to concerns about the tolerability of starting olanzapine abruptly at the 10mg qhs dose, we plan to administer only 5mg nightly for the first week of the “10mg” arm.

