#### **H. Concomitant Therapy**

Concomitant therapy of Parkinson’s disease including levodopa, carbidopa, selegiline, and dopamine agonists will be allowed if it satisfies the Inclusion and Exclusion Criteria given in section III.D.1. above. However, we will make every reasonable effort not to *change* the dose of any CNS-active medication during the 4 weeks of this study. The exception will be when we allow for upward titration of dopamimetics at the 2-week visit, if indicated.

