### **1.2. Safety and Safety Monitoring**

The primary safety measures will be UPDRS motor ratings, sleep log, and MMSE, in addition to a clinical Review of Systems on each visit. The Review of Systems is integrated into our routine patient care database. Significant **adverse events** will be reported to Lilly on standard forms. No routine clinical laboratory tests are anticipated.

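### Objective 3 states the tolerability comparison as 5 mg versus 10 mg only; motor harm common to both doses cancels in it, and no placebo comparison is stated for tolerability

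*Protocol*

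**What the plan says.** Protocol section II lists two primary and two secondary objectives. Placebo is named once, in the first primary objective, and for efficacy: "Determine whether olanzapine has superior efficacy to placebo in treating psychosis". The tolerability objective, the third, names only the two active doses: "Compare tolerability of 5mg and 10mg daily doses of olanzapine in this population".

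The other relevant sections are these:

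- Section I (Introduction / Rationale) gives unacceptable motor effects as the main failing of other antipsychotics in these patients. It criticises the earlier open study for having no placebo arm.
- Section III.A schedules full UPDRS at baseline, week 2 and week 4 in all three arms. It also says that "patients in the 10 mg arm will take only 5 mg nightly for the first week".
- Section III.B justifies the control arm by efficacy: "with the parallel group, placebo-controlled design, we can show whether olanzapine is superior to placebo in treating PD psychosis".
- Section III.D.2 promises a comparison across all three groups for efficacy.
- Section III.H makes one exception to stable CNS-active medication: "when we allow for upward titration of dopamimetics at the 2-week visit", if indicated.
- The safety section (1.2) says "The primary safety measures will be UPDRS motor ratings, sleep log, and MMSE", with a review of systems at each visit. It names no comparator.
- Section IV analyses 0-2 and 2-4 weeks as separate periods because dopamimetics may be added at week 2. The only dependent variable it names is the BPRS positive symptom subscale.

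**The concern.** The motor question that motivates the trial is whether olanzapine worsens parkinsonism. Answering it needs a group not taking the drug. The trial has one, but the stated tolerability comparison leaves it out. If both doses worsen motor function to a similar degree, 5 mg and 10 mg will look alike, and that likeness could be reported as acceptable tolerability.

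The dose contrast is also short of exposure. Both active arms take 5 mg in week 1, so at the 2-week visit the doses have differed for only one of the two weeks. After that visit, dopamimetic increases may differ by arm, so later motor change within an arm cannot stand in for a placebo comparison.

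A placebo contrast on motor score could still be run afterwards. If it is not stated in advance, it becomes a post-hoc choice on the central safety question.

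**Working it through.** **1. The plan's own figure.** Section III.D.2 states 90% power to detect a 50% improvement in total BPRS within one group of 10-11 patients at alpha 0.05. It cannot be reproduced, because the protocol gives neither the BPRS mean nor the SD. Solving backwards with the noncentral t (two-sided), it implies a within-group change of about 1.16 SD for n = 10 or 1.09 SD for n = 11. The figure concerns efficacy within one group, and nothing below depends on it. The protocol gives no power for tolerability.

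**2. Inputs.**
- From section III.D.2: 10 patients per arm, or 15 per arm if the extension is used (10 + 5), and alpha 0.05.
- Assumed: a two-sided test, and motor harm of d SD against placebo, since no UPDRS SD is given. A range of d is shown.

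**3. Why shared harm cancels.** Let the mean motor change be m on placebo and m + d on each dose.
- 10 mg minus 5 mg = (m + d) - (m + d) = 0 for every d. The test rejects with probability alpha = 5%, whatever the sample size.
- Pooled olanzapine minus placebo = (m + d) - m = d. One dose minus placebo is also d.

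**4. Power of the placebo contrasts.** For a two-sample t test the noncentrality is d / sqrt(1/n1 + 1/n2), on n1 + n2 - 2 degrees of freedom.
- Pooled, 20 versus 10: sqrt(1/20 + 1/10) = sqrt(0.15) = 0.387. At d = 1 the noncentrality is 1/0.387 = 2.58, with 28 df and critical value 2.048. Power is 70%.
- One dose, 10 versus 10: sqrt(1/10 + 1/10) = sqrt(0.20) = 0.447. At d = 1 the noncentrality is 1/0.447 = 2.24, with 18 df and critical value 2.101. Power is 56%.

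| Assumed equal harm d (SD) | 5 mg v 10 mg | One dose v placebo, 10 per arm | Pooled v placebo, 10 per arm | Pooled v placebo, 15 per arm |
|---|---|---|---|---|
| 0.5 | 5% | 18.5% | 24% | 34% |
| 0.8 | 5% | 40% | 51% | 70% |
| 1.0 | 5% | 56% | 70% | 87% |
| 1.2 | 5% | 72% | 85% | 96% |

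A contrast within the three-arm ANOVA (1 and 27 df) gives the same pooled figures for 10 per arm, to the nearest percent.

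**5. If harm rises with dose.** Suppose 0.5 SD at 5 mg and 1.0 SD at 10 mg (assumed). The dose contrast then has a true difference of 1.0 - 0.5 = 0.5 SD and, by the same 10-versus-10 formula, 18.5% power. The 10 mg versus placebo contrast has d = 1.0 and 56% power.

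**6. Precision.** The expected 95% half-width is the critical value times the root term: 2.101 x 0.447 = 0.94 SD for dose versus dose, and 2.048 x 0.387 = 0.79 SD for pooled versus placebo. An observed difference of zero between doses would still leave differences of nearly 1 SD inside the interval.

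**The case against.** The strongest reply has five parts.

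- **The data are there.** UPDRS is scheduled in all arms, and the safety section does not exclude placebo. This stands. A reader might infer that the trial cannot reveal motor harm shared by both doses. The documents do not support that: the limit belongs to the comparison stated in Objective 3, not to the data.
- **Contrasts on safety variables belong in an analysis plan.** This stands for covariates, models and intervals, and an analysis plan may add the placebo comparison. But the objective itself is fixed in the protocol, and it names two active doses.
- **Dose versus dose is a proper question.** This stands. It matches the second primary objective and the tolerability concern behind the run-in, under which "we plan to administer only 5mg nightly for the first week". If harm rises with dose, the contrast is informative, though weak at this size.
- **The dopamimetic problem is already recognised.** This stands. A reader might infer that the plan relies on a 4-week motor comparison blurred by dopamimetic changes. Section IV separates the two periods for exactly that reason, and no section proposes such a comparison.
- **Functional measures are compared with placebo.** This stands in part. Schwab-England, UPDRS ADL and PDQ-39 are secondary efficacy measures, and efficacy is to be compared across all three groups. Disabling harm could show there, but these are not the UPDRS motor score named for safety.

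**Conclusion.** The point holds as a gap in a stated objective. Objective 3 sets an active-only comparison, no other section states a placebo comparison for tolerability or motor safety, and harm common to both doses cancels in what is stated.

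The cancellation is algebra and needs no assumption about size. The power figures do rest on assumptions: equal harm at both doses, the chosen d, a two-sided 5% test, and complete data. A reader might take 5% against 70% as the measured loss. It is not: equal harm is the case least favourable to the dose contrast and most favourable to pooling, 1 SD is an assumed value, and one dose versus placebo reaches only about 56% at that value. The figures show that the placebo contrast carries information on shared harm where the dose contrast carries none. They do not show that this trial would settle the question.

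Nor does the protocol say that a non-significant dose difference will be read as good tolerability. That is a risk in later reporting, which clearer wording would remove.

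**What to change.** - Reword Objective 3 to compare the tolerability of olanzapine with placebo, both doses pooled and then each dose, and then 10 mg with 5 mg. The dose question is kept.
- Name the 0-2 week change in UPDRS motor score, adjusted for baseline, as the main tolerability measure. This follows the period split already in section IV and uses scores that precede any planned dopamimetic increase.
- Report estimates with confidence intervals for every contrast, so that a non-significant result is not taken as evidence of good tolerability. Show MMSE and withdrawals by arm, and show 4-week motor scores together with dopamimetic changes.

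No new visits, measurements or patients are needed, and dosing and clinical management are untouched. The cost is wording plus three placebo contrasts (pooled, 5 mg, 10 mg). Power will be limited: at 10 per arm, the pooled contrast has about 51% at 0.8 SD and 24% at 0.5 SD.

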## **III. Investigational Plan**

### **A. Summary of Study Design**

Patients will be screened and if they meet the criteria given in section III.D.1. will enter into one of three arms, shown as three rows of the table below. Each arm will consist of nightly

(qhs) dosing of matched tablets or capsules containing 0, 5, or 10 mg of olanzapine. However, patients in the 10 mg arm will take only 5 mg nightly for the first week.

See the table below for a diagrammatic summary of the study design.

| baseline                          | 1st week | 2nd week | 2-wk visit                                                      | weeks 3-4 | 4-wk visit                                                 |
|-----------------------------------|----------|----------|-----------------------------------------------------------------|-----------|------------------------------------------------------------|
| clinical evaluation;
randomize | placebo  | placebo  | clinical evaluation;
increase
dopamimetic if
indicated | placebo   | clinical evaluation;
return to routine
clinical care |
|                                   | 5mg      | 5mg      |                                                                 | 5mg       |                                                            |
|                                   | 5mg      | 10mg     |                                                                 | 10mg      |                                                            |

Baseline evaluation:

Psychiatric, neurologic and general medical history and examination; Clinical Global Impression (CGI) by MD, PDQ39 (a brief, self-rated overall quality of life questionnaire), videotaped psychiatric interview for later blinded BPRS (Brief Psychiatric Rating Scale) rating, Schwab-England ADL assessment, full UPDRS (Unified Parkinson's Disease Rating Scale), MMSE (Folstein Mini-Mental State Examination), HDRS (Hamilton Depression Rating Scale), Beck depression inventory (Beck), patient- or caretaker-reported sleep hours/quality

Interim evaluation:

clinical evaluation; CGI (MD, pt, caretaker), videotaped psychiatric interview for later blinded BPRS, Schwab-England, full UPDRS, MMSE, pill counts, PDQ39, Beck, sleep hours

Final evaluation:

clinical evaluation; CGI (MD, pt, caretaker), videotaped psychiatric interview for later blinded BPRS, Schwab-England, full UPDRS, MMSE, pill counts, PDQ39, Beck, sleep hours

**B. Rationale for Design and Control**

Our design can significantly strengthen the conclusions of Wolters et al. (1996) in three ways. First, with the parallel group, placebo-controlled design, we can show whether olanzapine is superior to placebo in treating PD psychosis. Second, with a fixed dose design we can address the question of optimal olanzapine dose in these patients. Third, the Wolters et al study did not use blinded ratings of psychosis. To address this, we will videotape clinical interviews at each study visit. The main outcome measure, BPRS ratings of psychosis, can then be rated after the end of the study by an investigator who will be blind not only to olanzapine dose but also to duration of treatment (0, 2, or 4 weeks). This will allow us to show that improvement in any treatment group is not due to investigator or patient expectation of improvement, and may also increase our power as the placebo group may show less change.

We chose 4 weeks rather than a longer study period because clinical experience and the Wolters et al. trial both suggest that improvement in psychosis is usually seen by this point.

The doses chosen are due in part to the desire to bracket the mean final dose in the open study (7mg/day), and in part to the fact that olanzapine is marketed in 5mg and 10mg tablets.

A placebo control is not only scientifically needed but also ethically justified, given the potential side effects of either olanzapine or other treatments of psychosis in this population (beyond the conservative measures we require for study entry).

### **C. Investigator Information**

Please see the CVs submitted separately.

#### **1. Responsibility for Authorship of Clinical Study Report**

The principal investigator, [name]., will author the study report.

### **D. Study Population**

#### **1. Criteria for Enrollment**

##### **a. Inclusion Criteria**

- age 30 years and above
- male or female
- clinical diagnosis of idiopathic Parkinson's disease
- currently experiencing hallucinations, delusions or formal thought disorder (*i.e.* score > 3 on one of the corresponding BPRS items)
- current treatment with dopamimetics
- dopamimetic dosing already at lowest clinically acceptable level (due to needed mobility, etc.)
- availability of family member / caretaker who can reliably report symptoms
- ability to give informed consent, or appropriate substituted consent available
- native or near-native command of English

##### **b. Exclusion Criteria**

- MMSE score < 20
- current clinical diagnosis of delirium, unless clearly related only to dopamimetics
- NMS-like syndrome or catatonia
- other concurrent CNS illness, *e.g.* stroke
- current systemic illness likely to affect the CNS, *e.g.* lupus or untreated hypothyroidism
- significant surgical or general medical intervention expected within the next 6 weeks
- history of sensitivity to olanzapine
- antipsychotic use within the last month (6 months for depot neuroleptics)
- pregnancy

#### **2. Sample Size and Statistical Justification**

Sample size will be 10 patients per arm (30 total). Using the Wolters et al baseline data as a rough estimate of variance, a power analysis shows that we would have a 90% likelihood of detecting a 50% improvement in total BPRS scores (at  $\alpha = 0.05$ ) within a single treatment group of 10-11 patients. From the same data, power would be slightly higher using the BPRS "positive item" subscale (*i.e.*, the 4 items which reflect hallucinations, delusions, or formal thought disorder).

To rigorously estimate power for our study design would require an estimate of the variance in the *change* of BPRS scores with olanzapine (or placebo). We do not have that data. However, we suspect on clinical grounds that there will be no meaningful improvement in the placebo group (here is where the blinded videotape ratings may add to our power), so we expect to also find a significant difference between groups, using a comparable number of patients per treatment arm. Efficacy will be compared across all 3 groups.

Due to some uncertainty about the power of the study as described above, we have the following backup plan. After enrolling 30 patients, we plan to submit the primary outcome data, together with the sealed code for unblinding the data, to a statistical consultant who will not otherwise participate in the study. If statistically significant differences in efficacy are apparent among the 3 arms at this point (*i.e.*,  $p < 0.01$ , ANOVA), we will conclude enrollment and further analyze the results. Otherwise we will seek to enroll an additional 5 subjects in each arm before we are informed of the study code.

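### The 90% power quoted for 10 per arm is at alpha 0.05 for a within-group change, but the decision test at 30 patients is a three-arm ANOVA at p < 0.01, so the 90% does not describe the chance of finishing at 30

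*Protocol*

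**What the plan says.** All of this is in Protocol section III.D.2 (Sample Size and Statistical Justification).

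- **Size and support.** The size is 10 per arm, 30 in total. The supporting statement is "a power analysis shows that we would have a 90% likelihood of detecting a 50% improvement in total BPRS scores", at alpha = 0.05, and it applies "within a single treatment group of 10-11 patients". The variance comes from the cited open study, using its "baseline data as a rough estimate of variance". No BPRS mean, SD, test or sidedness is given.
- **Caveat.** A rigorous power estimate for the actual design "would require an estimate of the variance in the *change* of BPRS scores with olanzapine (or placebo). We do not have that data". The authors still expect a between-group difference with similar numbers per arm, because "we suspect on clinical grounds that there will be no meaningful improvement in the placebo group".
- **Decision rule at 30.** A backup plan, introduced because power is uncertain, has an outside statistical consultant compare the arms. "If statistically significant differences in efficacy are apparent among the 3 arms at this point", defined as p < 0.01 by ANOVA, enrolment ends. If not, five more patients per arm are sought, which makes 45.

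Section IV (Data Analysis Methods) refers back to this rule. No power is given for the ANOVA at 0.01, and neither power nor a significance level is given for an analysis at 45.

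**The concern.** The one power figure offered for 10 per arm and the one decision test specified at 10 per arm differ in two ways. The power figure is for a change within one group, while the test compares three groups. The power figure uses alpha 0.05, while the test requires p < 0.01. Each difference lowers power.

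The protocol's caveat covers the first difference in part, through the unknown variance of change. It does not mention the second, although the cost of a stricter threshold can be worked out without any variance data. A reader who plans recruitment, drug supply or ethical review from this section could take 30 patients as well supported, when the chance of finishing there may be much lower than the figure printed beside it.

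**Working it through.** **Inputs from section III.D.2:** 10 per arm and three arms; 90% power at alpha 0.05 in a group of 10-11; no placebo improvement expected; ANOVA at p < 0.01 at 30 patients; 15 per arm if extended.

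**Assumptions, because the protocol gives no mean, SD, test or sidedness:** a t-test lies behind the 90%; the ANOVA is one-way; the same SD applies to the between-arm comparison; placebo change is 0; the 5 mg arm has either the full effect or half of it.

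**Step 1. The stated figure.** The 90% cannot be reproduced from the protocol's inputs. Instead, solve for the standardised effect d that gives exactly 90% at alpha 0.05 (noncentral t).
- One-sample (paired) reading: noncentrality d√n, n − 1 degrees of freedom. Example, n = 10, two-sided: d = 1.155, noncentrality 1.155 × √10 = 3.65.
- Two-sample reading: noncentrality d√(n/2), 2n − 2 degrees of freedom. Example, n = 10, two-sided: d = 1.534.

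**Step 2. Change only the threshold.** Keep test, n and d, and move alpha from 0.05 to 0.01 (next-to-last column but one below). In the first example the critical t (9 df) rises from 2.26 to 3.25 and power falls from 90% to 65.5%.

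**Step 3. Use the test the protocol specifies.** For the three-arm ANOVA with 10 per arm, noncentrality is λ = 10 × Σ(μᵢ − μ̄)². With means (0, d, d), λ = 10 × (2/3)d²; with means (0, d/2, d), λ = 10 × d²/2. The degrees of freedom are 2 and 27, and the critical F is 3.35 at 0.05 and 5.49 at 0.01. For d = 1.155, λ = 8.89 and 6.67.

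| Reading of the 90% | d | Same test at 0.01 | ANOVA at 0.05: full / half effect at 5 mg | ANOVA at 0.01: full / half effect at 5 mg |
|---|---|---|---|---|
| One-sample, 2-sided, n = 10 | 1.155 | 65.5% | 71% / 58% | 45% / 32% |
| One-sample, 2-sided, n = 11 | 1.087 | 66.5% | 66% / 53% | 39% / 27% |
| One-sample, 1-sided, n = 10 | 1.005 | 64.4% | 59% / 46% | 32% / 22% |
| One-sample, 1-sided, n = 11 | 0.950 | 65.3% | 54% / 42% | 28% / 19% |
| Two-sample, 2-sided, n = 10 | 1.534 | 70.4% | 93% / 84% | 77% / 61% |
| Two-sample, 2-sided, n = 11 | 1.454 | 70.8% | 90% / 79% | 71% / 55% |
| Two-sample, 1-sided, n = 10 | 1.361 | 68.7% | 85% / 73% | 64% / 47% |
| Two-sample, 1-sided, n = 11 | 1.293 | 69.1% | 81% / 69% | 58% / 42% |

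The threshold alone costs about 19-26 points (90% to 64-71%). A normal approximation gives 75%. The ANOVA at 0.01 has 19-45% power on the one-sample reading and 42-77% on the two-sample reading.

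**Step 4. Split the loss** (d = 1.155). With the full effect at 5 mg, moving from the within-group test to the ANOVA at 0.05 takes 90% to 71% (19 points), and the threshold takes it on to 45% (26 points). With half the effect, the steps are 90% to 58% (32 points) and 58% to 32% (26 points). Both causes matter.

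**Step 5. Sensitivity to the SD of change.** Suppose d = 1.155 is in baseline-SD units and the SD is the same at both visits. Then SD of change = SD of baseline × √(2(1 − r)), where r is the baseline-to-follow-up correlation, and the effect in SD-of-change units is d/√(2(1 − r)).

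| r | SD of change / baseline SD | ANOVA at 0.01, full effect at 5 mg | half effect |
|---|---|---|---|
| 0.3 | 1.18 | 30% | 21% |
| 0.5 | 1.00 | 45% | 32% |
| 0.7 | 0.77 | 74% | 58% |
| 0.8 | 0.63 | 92% | 80% |

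The chance of extending, which is one minus these values, therefore runs from about 8% to about 80%.

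**The case against.** The strongest reply is that the protocol does not claim 90% for its design. It limits the figure to a within-group change, says the data needed to power the design are lacking, and adds a conditional extension because power is uncertain. That stands. A reader might infer that the trial is presented as having 90% power for its between-arm comparison, or that the larger size is concealed; the text supports neither. What remains is that the 90% is the only figure printed in support of 10 per arm, and that the caveat is about variance, not about the stricter threshold.

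A second reply is that a strict first look with low power is normal in a design that can extend. That also stands. If the final test at 45 used 0.05, which is an assumption, the two-stage rule simulates at about 89% or 79% overall power for d = 1.15 (full or half effect at 5 mg), and at about 99% or 96% for d = 1.53. But adequate power would then come from 15 per arm, while the protocol attaches its figure to 10.

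A third reply is that the size of the shortfall rests on an SD the documents do not give. This is correct. A reader might infer that 45 is the likely size. The one-sample reading with equal SDs points that way (55-81% chance of extending), but the two-sample reading gives 23-58%, and a correlation of 0.8 gives as little as 8%. The protocol also says power is slightly higher on the positive-item subscale, which section IV uses as its dependent variable; the figures above make no allowance for that.

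**Conclusion.** The point holds as a mismatch between the stated power and the stated decision rule. The fall from 90% to about 64-71% for the within-group test needs no SD; it assumes only that a t-test lies behind the 90%. The ANOVA figures of 19-45% and 42-77% rest on no placebo change, the same SD between arms, and an effect back-solved from the 90%. Under those assumptions no variant reaches 90%. A figure near 90% needs an SD of change well below the baseline SD, for example a ratio of about 0.63 on the one-sample reading with both doses at full effect.

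Three stronger readings are not supported. The documents do not show that extension to 45 is expected. The threshold is not the only cause, because the within-group basis of the 90% costs a similar amount. And 65% is not the chance of stopping at 30: it is the power of a one-sample test that the decision rule does not use.

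**What to change.** Revise section III.D.2 as follows:

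- Stop using the 90% at alpha 0.05 as the support for 30 patients.
- State the power of the three-arm ANOVA at p < 0.01 with 10 per arm, over a range of SDs of change and for stated patterns of effect across the two doses.
- State the power and the significance level of the analysis at 15 per arm.
- Describe 45 as the planned maximum, without saying that extension is expected and without giving 65% as a stopping probability.

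The cost is a rewrite of one section and a short table. The section would show a less favourable figure for the 30-patient look. Trial procedures do not change, and no patients are added beyond the 45 already foreseen.
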